**Methods:**

In phase 1 (Human Research Ethics Committee [Medical] of the University of the Witwatersrand [220813, Johannesburg, South Africa] and the Massachusetts General Brigham Institutional Review Board [2022P002765, Boston, Massachusetts, United States]), we conducted 3 focus group discussions to solicit feedback on the lived experiences of stress, sources of stress, impact on job functioning, coping strategies, the proposed intervention, and recruitment strategies for nurses. These data informed adaptations to the intervention. In phase 2 (Human Research Ethics Committee [240106, Johannesburg, South Africa]; Massachusetts General Brigham Institutional Review Board [2024P001407, Boston, Massachusetts, United States]), we conducted a small proof-of-concept study (N=8) with preintervention and postintervention assessments, 6 intervention sessions with a nurse interventionist, and a qualitative exit interview. Following appropriate adaptations, we conducted a pilot randomized controlled trial (N=60) in which participants were randomized to the intervention or the control condition. The control condition received a one-time, 90-minute didactic stress management session. The intervention condition consisted of two 4-hour group skills-based sessions on the relaxation response, components of stress, recuperative sleep, mindful awareness, resilience, and social support. Sessions included practice-based exercises and videos to complement the intervention materials. Baseline, posttreatment (intervention only), and follow-up assessments, as well as qualitative exit interviews (n=15, intervention only), were conducted. Primary outcomes are feasibility (number screened, eligible, and enrolled; the number of treatment sessions and assessments completed in the intervention arm; assessment duration; and reasons for declining enrollment and prematurely leaving the trial) and acceptability (Client Satisfaction Questionnaire-8 and qualitative data).

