##### Group Assignment

After completion of the small proof-of-concept study, the randomized pilot study (N=60 nurses) was conducted. Once participants were screened, they were asked to select their availability based on 4 possible dates, which were randomly assigned as intervention or control. The groups consisted of approximately 10 participants each.

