### Data Collection

#### Assessment Instruments

Intervention participants were asked to complete 3 quantitative assessments (baseline assessment at enrollment [ie, prerandomization], a posttreatment assessment, and a final follow-up assessment at around the 3-month time point). Participants completed a qualitative exit interview (n=15) between the posttreatment and follow-up assessments. Control participants were asked to complete assessments at baseline and at approximately 3 months. Baseline assessments lasted approximately 45 minutes, and posttreatment and follow-up assessments each lasted approximately 35 to 40 minutes (see Table 2 for the list of instruments used at each assessment).

**Table 2. T2:** Measures included at each major assessment.

Instruments	Baseline assessment	Posttreatment assessment	Follow-up assessment
Sociodemographics^a^	✓	—^b^	—
Resilience: Measure of Current Status (MOCS-A); Current Experiences Scale (CES) [51]	✓	✓	✓
Perceived stress: Perceived Stress Scale (PSS-10) [52,53]	✓	✓	✓
Burnout: Maslach Burnout Inventory Human Services Survey for Medical Personnel (MBI-HSS [MP]) [22]	✓	✓	✓
Absenteeism^a^	✓	✓	✓
Compassion fatigue: Professional Quality of Life Scale (ProQOL) Version 5 [54]	✓	✓	✓
Stigma: Measuring HIV Stigma and Discrimination Among Health Facility Staff: Standardized Brief Questionnaire [55]	✓	—	—
Anxiety: Generalized Anxiety Disorder (GAD-7) scale [56]	✓	✓	✓
Depression: Patient Health Questionnaire (PHQ-9) [57]	✓	✓	✓
Social support: Coping Orientation to Problems Experienced (COPE) Inventory [58]	✓	✓	✓
Optimism: Life Orientation Test – Revised (LOT-R) [59]	✓	✓	✓
Distress tolerance: Distress Tolerance Scale (DTS) [60]	✓	✓	✓
Acceptability: Client Satisfaction Questionnaire (CSQ-8) [61]^c^; Qualitative exit interviews^c^	—	✓	—
Adherence to Weekly Intervention Practice Exercises^a^^c^^d^	—	✓	✓

a Instrument developed by study team.

b Not available.

c Only for intervention arm.

d Will provide the research team with an understanding of whether intervention skills were implemented in nurse’s daily lives outside of the intervention setting and may be used to generate a rating of adherence to out-of-session practice guidelines during study analyses.

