### Data Analysis

The sample size (N=60) was chosen based on studies of similar scope (eg, other pilot behavioral trials funded via the same mechanism) and established guidelines for pilot behavioral studies to establish feasibility [62-64].

To evaluate feasibility as a coprimary outcome, we will assess the number of nurse participants screened, eligible, and enrolled (ie, whether >70% of those screened enroll/agree to participate); the number of treatment sessions (ie, whether >70% of participants randomized to the intervention complete at least 2 out of 3 sessions) and assessment visits completed (ie, whether >70% of all participants complete at least 2 out of 3 assessments) in the intervention arm; assessment duration; and reasons for declining enrollment and prematurely leaving the trial. Acceptability (second primary outcome) will be evaluated using the Client Satisfaction Questionnaire (CSQ-8) [61] and qualitative exit interview data among intervention arm participants. Scores on the CSQ-8 will be categorized into 4 levels of satisfaction: ‘‘poor’’ (score 8‐13), ‘‘fair’’ (score 14‐19), ‘‘good’’ (score 20‐25), and ‘‘excellent’’ (score 26‐32). All qualitative exit interview data will be explored for categories and themes around intervention acceptability. Qualitative data will be analyzed using content analysis, facilitated by the Dedoose software [65], to organize data and facilitate analyses. Two study team members will independently review the transcripts to generate an overarching thematic framework for data interpretation, in which major and minor themes are identified. Thematic frameworks will then be compared for consistency, and discrepancies will be discussed until agreement is reached. Data will be reexamined, messages will be extracted and highlighted, and ongoing discussion between coders will allow for further theorizing and making interconnections between research questions, coding categories, and raw data [66].

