With respect to exploratory evaluations of quantitative data and secondary outcomes, we expect to compare each outcome between groups using mixed model regression analyses, with participant ID as a random effect. Fixed covariates will include assessment time point (baseline, posttreatment assessment, and 3-month follow-up) and years working in HIV care. Other covariates, such as education, age, and baseline levels of stress, anxiety, and depressive symptoms, and clinic characteristics (eg, clinic size, availability of equipment, and urban vs peri-urban) will also be considered. We will consider exploratory mediational and moderational analyses, based on procedures outlined by Hayes [67]. We will examine patterns in missing data to see if missingness is related to measured participant characteristics. We will adjust for missing data using multiple imputation, as appropriate. We will also adjust for multiple comparisons using the method of Hothorn et al [68].

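### The random arm was given to four session dates, not to nurses, yet the article describes randomised participants and the between-arm model has no date or availability term

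*Protocol article*

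**What the plan says.** The Abstract (Methods) states that "participants were randomized to the intervention or the control condition". Data Analysis likewise sets its session-completion threshold among participants randomised to the intervention.

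Group Assignment gives the mechanism: once screened, nurses "they were asked to select their availability based on 4 possible dates, which were randomly assigned as intervention or control". It adds that "The groups consisted of approximately 10 participants each". It does not say when the dates received their arms, when nurses learned them, or how a nurse free on several dates was placed. Assessment Instruments describes the first assessment as a "baseline assessment at enrollment [ie, prerandomization".

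For the arm comparison, Data Analysis expects to "compare each outcome between groups using mixed model regression analyses, with participant ID as a random effect". The only fixed covariates it commits to are the assessment occasion and length of experience in HIV care. Education, age, baseline stress, anxiety and depressive symptoms, and clinic characteristics are to be considered as further covariates. Session date, availability and employment status are not named. The same paragraph labels these comparisons exploratory or secondary.

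**The concern.** When individuals are randomised, each nurse's arm is independent of her circumstances, and imbalance shrinks as the sample grows. When dates are randomised and nurses attach to dates by availability, imbalance shrinks only with the number of dates. A nurse free on one date has her arm fixed by her diary and that date's label.

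Availability is unlikely to be neutral here. The Introduction links workload and staff shortage to stress and absenteeism. The section on refinement of the intervention says recently laid-off nurses were admitted, and their free time plausibly differs from that of working clinic staff. Stress, burnout and absenteeism are all measured outcomes. A difference between arms at 3 months could therefore partly reflect who could attend which date, while the reported precision would be that of 60 independently allocated nurses. Study Aims says the pilot tests its procedures ahead of a larger trial, so a wrong design label could be carried forward.

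**Working it through.** **Setting the passages side by side.** The Abstract has participants randomised; Group Assignment has dates randomised and nurses stating availability on them. No passage describes random placement of individual nurses among the dates they could attend. On the text, the randomised unit is the date.

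**The plan's own figure.** "The sample size (N=60) was chosen based on studies of similar scope" and on pilot-study guidelines. No alpha, power, effect size or SD is given, so N=60 cannot be reproduced and is not disputed here. The group structure is unclear: 4 dates × 10 = 40, whereas 60/4 = 15 per date and 60/10 = 6 groups.

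**Number of possible allocations** (equal split assumed).
- 4 dates, 2 v 2: C(4,2) = 6; smallest two-sided randomisation p-value 2/6 = 0.33.
- 6 groups, if each were a separately randomised unit, 3 v 3: C(6,3) = 20; smallest p-value 2/20 = 0.10.

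**Why more nurses per date do not help.** Let ρ be the share of outcome variance lying between dates, from whatever source (who attends, or what happens in the group). With 2 v 2 dates of m nurses and total variance 1, the variance of the arm difference is

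ρ + (1 − ρ) × 2/(2m).

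The second term falls as m grows; the first does not. The document gives no ρ, so 0.01 to 0.10 is an assumption.

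| Assumed ρ | SD of arm difference, m = 15 (N=60) | SD, m = 30 (N=120) | Floor √ρ |
|---|---|---|---|
| 0 | √(2/30) = 0.26 | √(2/60) = 0.18 | 0 |
| 0.01 | √(0.01 + 0.066) = 0.28 | √(0.01 + 0.033) = 0.21 | 0.10 |
| 0.05 | √(0.05 + 0.063) = 0.34 | √(0.05 + 0.032) = 0.29 | 0.22 |
| 0.10 | √(0.10 + 0.060) = 0.40 | √(0.10 + 0.030) = 0.36 | 0.32 |

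**Effect of leaving date out of the analysis.** A nominal 5% two-sample t-test ignoring date, simulated with 40,000 replicates, rejected a true null in these percentages of runs:
- 4 dates of 15: 6.7%, 13.5% and 21.2% at ρ = 0.01, 0.05 and 0.10.
- 6 groups of 10: 5.9%, 10.3% and 15.8%.

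These figures show how the result moves with ρ; they do not estimate what happened in this trial. They use a single outcome measurement without baseline adjustment, which the trial's model could improve on.

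**The case against.** The strongest case on the other side has five parts.

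1. **Timing.** A reader might infer that dates were labelled first and nurses then sorted themselves into arms. The text does not say so. Collecting availability, then baseline, then assigning dates fits both Group Assignment and the prerandomisation wording. Neither self-selection nor an error in that wording is shown. This stands.
2. **Session length.** A reader might infer that availability differed by arm because two 4-hour sessions demand more than one 90-minute session. Nurses chose dates, not arms; length could matter only if they knew the labels or committed to arm-specific time. This stands.
3. **Size.** One could posit a 20- or 40-point gap in a characteristic worth 0.5 SD and report 0.20 × 0.5 = 0.10 SD or 0.40 × 0.5 = 0.20 SD as bias. Both inputs are invented. Even individual randomisation of 30 v 30 with 50% prevalence gives a difference with SD √(0.25 × 2/30) = 0.129, so a 20-point gap would occur about 12% of the time. No such figure should be attached to this trial, nor should imbalance be called likely. This stands.
4. **Mitigation.** The model includes baseline as a time point, and baseline symptoms and clinic characteristics may be added from an open list. This stands in part: the further covariates are optional, and none represents the date as the randomised unit.
5. **Reach.** Enrolment counts, session completion, satisfaction scores and exit interviews involve no contrast between arms, and the mechanism is openly disclosed. This stands, and it limits the importance of the point.

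None of this removes the gap between a date-randomised design and a model and label that treat nurses as the randomised unit.

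**Conclusion.** The point holds in a limited form. Group Assignment makes the session date the randomised unit, while the participant-randomised wording and the between-group model do not reflect this. If selection was blind to labels, the consequence is chance confounding and understated uncertainty, not systematic bias. If labels were known, self-selection is an additional possibility. The document does not decide between these.

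The size in this trial cannot be estimated, because between-date variation is not reported; the tabulated values rest on assumed ρ, equal arms and a 2 v 2 split of dates. The effect is confined to the exploratory arm comparisons. A reader should not conclude that the feasibility or acceptability results are compromised, or that arm differences are biased in a known direction. The point is worth acting on because it changes what the arm comparison can support and, per Results, analysis is still in progress.

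**What to change.** - Describe the design as allocation by randomised session date wherever participants are said to be randomised, and state the number of dates and groups so that they agree with N=60.
- State whether dates were assigned, and revealed, before or after date selection and baseline, and how nurses free on several dates were placed. Correct the prerandomisation wording if needed.
- Tabulate baseline characteristics by date as well as by arm.
- Commit to adjusting the arm comparison for the baseline value of the outcome and, where recorded, employment status.
- If availability selections were kept (the article says nurses were asked, not that answers were retained), add a sensitivity analysis in nurses available on at least one intervention and one control date. Keep this simple: four dates allow 2⁴ − 1 = 15 non-empty availability patterns, too many to stratify fully with 60 nurses.
- Present arm contrasts as descriptive. Four dates in two arms leave 4 − 2 = 2 degrees of freedom between dates, so a date random effect would be poorly estimated and cannot replace this caution.

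The cost is wording, one table and a modest analysis, with no new data collection. The price is a less favourable design label and a smaller n in the sensitivity subset.

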##### Control Condition

The control condition received a 1-time, approximately 90-minute, interventionist-led didactic stress management session (with no interventionist follow-up). The session provided information on the 4-component model of stress and an “energy battery” exercise, which asked participants to reflect on stressors and things that offset stress (Textbox 1).

Textbox 1. Stress management session content for control arm.The science of mind-body medicineThe stress responseThe flight-or-flight responseResiliencyCognitive behavioral therapy model of emotionThe energy battery

##### Intervention Condition

The intervention condition consisted of two 4-hour interventionist-led group sessions. The sessions provided information on topics including the RR, the components of stress, recuperative sleep, mindful awareness, resilience, and social support (see Table 1). Sessions also included practice-based exercises (eg, breathing exercises and mindfulness exercises). Short videos were recorded and included in the sessions to complement the material on breathing, thought records (ie, a practical way to capture and examine thoughts), energy battery (ie, awareness of things that add to or deplete their personal battery), social support, mindfulness, and RR exercises. Participants were provided with a manual describing session content and audio recordings of RR exercises. Participants were encouraged to complete practice notes between and after sessions, which corresponded with intervention modules (eg, relaxation practice) to document their goals and progress.

**Table 1. T1:** Adapted Stress Management and Resiliency Training-Relaxation Response Resiliency Program chapters and goals for the intervention arm.

Chapter title	Goals
Stress management and resiliency training	Introduce the SMART-3RP^a^ Introduce the Science of Mind-Body Medicine and its components: Stress Response, the Fight-or-Flight Response, and the RR^b^ Introduce Stress Management and Resiliency Training goals strategy Introduce RR-elicitation method: single pointed focus meditation, body and breath awareness, letter to yourself exercise Establish program and weekly goals
The RR	Introduce RR-elicitation method: autogenic training Introduce “MINIs”^c^ as a method to reduce tension and anxiety throughout the day Introduce the concept of appreciation Discuss recuperative sleep and sleep tips Introduce the Stress Warning Signals exercise
Stress awareness	Introduce mindfulness Introduce RR-elicitation method: mindful awareness MINI^c^ Learn the types of social support Identify what you need and what is feasible Discuss empathy and compassion
Mending mind and body	Introduce new RR-elicitation method: chair yoga Use strategies for applying mindful awareness in daily living Introduce the Pause, Breathe, Reflect, and Choose routine Reflecting on what’s important exercise
Creating adaptive perspective	Introduce new RR-elicitation method: loving kindness meditation Use cognitive reappraisal as a way to build adaptation Discuss negative automatic thoughts and thinking errors Learn about different coping styles: problem-solving and acceptance-based coping Explore the development of acceptance, an essential quality of acceptance-based coping
Promoting positivity	Introduce RR-elicitation method: idealized self Identify how positivity can increase resiliency in the long term Learn concepts and strategies for enhancing positivity Review SMART-3RP strategies learned Develop a plan for continuing to use program strategies Set goals for the future

a SMART-3RP: Stress Management and Resiliency Training-Relaxation Response Resiliency Program.

b RR: relaxation response.

c MINI: Mindfulness, Intention-setting, Nurture a hobby, Indulge in gratitude.

Participants also had the option of accessing a closed (eg, limited to group members from their cohort) WhatsApp group moderated by the interventionist. The interventionist initiated chats in between group sessions to provide support to participants in practicing stress management skills (eg, “What skills have you been able to practice?” and “Is there a skill that you need some support in using?”). In addition, the interventionist shared the recordings of the RR exercises and the short videos in the WhatsApp group on a weekly basis as a reminder to practice the RR exercises and maintain engagement with the participants.

All intervention sessions were delivered by a professional nurse who was trained on the intervention material and closely supervised by a clinical psychologist. Training sessions took place during the weeks leading up to and during the intervention delivery to review and practice the intervention content and to discuss strategies for delivering the intervention and facilitating group member comfort, participation, and cohesion. The interventionist offered 2 booster sessions, at approximately 1 month from the conclusion of session 2, to reinforce the intervention content and resiliency strategies. Participants were asked to sign a confidentiality statement prior to the inception of group sessions.

##### Fidelity

All sessions with the interventionist were audiotaped. Monitoring of the intervention will take into account both the interventionist’s adherence to the session material (eg, degree of coverage of session components) as well as competence [50] in delivering the material (eg, adherence to therapeutic skills, such as encouraging an environment of safety and encouraging discussion). Fidelity ratings will be completed using a checklist developed by the study team (see Multimedia Appendix 3). At least 10% of the sessions will be reviewed for fidelity by a study team member ([name]) with expertise in intervention strategies.

##### Retention

All study participants completed the Participant Locator Form, which collects their contact information, including social networks such as WhatsApp. Additionally, participants were asked to provide the contact information of 3 people to be contacted in the case that the research team failed to reach them. The research team tracked participants for follow-up visits and retention using phone calls and WhatsApp messages. The participants’ work schedules at the clinics were taken into consideration when scheduling phone calls and messages. Retention procedures were reviewed weekly by the Project Director and Principal Investigator.

##### Remuneration

Participants were reimbursed US $26 (R450) per study visit for their time, inconvenience, and transportation costs, as per South African Health Products Regulatory Authority guidelines.

##### Adverse Event Reporting

Adverse events are defined as harmful occurrences to participants, either study-related or non–study-related. Study staff were trained to make appropriate referrals for clinical care in consultation with the Principal Investigators. Adverse events meeting reporting criteria were reported as appropriate and were discussed during biweekly calls between the study Principal Investigator, recruiting site Principal Investigator, and Project Director.

##### Criteria for Discontinuation

Participants were informed that they could end study participation at any time if they desired and that withdrawal from the study would not impact their ongoing position at the health clinic facility.

### Data Collection

#### Assessment Instruments

Intervention participants were asked to complete 3 quantitative assessments (baseline assessment at enrollment [ie, prerandomization], a posttreatment assessment, and a final follow-up assessment at around the 3-month time point). Participants completed a qualitative exit interview (n=15) between the posttreatment and follow-up assessments. Control participants were asked to complete assessments at baseline and at approximately 3 months. Baseline assessments lasted approximately 45 minutes, and posttreatment and follow-up assessments each lasted approximately 35 to 40 minutes (see Table 2 for the list of instruments used at each assessment).

**Table 2. T2:** Measures included at each major assessment.

Instruments	Baseline assessment	Posttreatment assessment	Follow-up assessment
Sociodemographics^a^	✓	—^b^	—
Resilience: Measure of Current Status (MOCS-A); Current Experiences Scale (CES) [51]	✓	✓	✓
Perceived stress: Perceived Stress Scale (PSS-10) [52,53]	✓	✓	✓
Burnout: Maslach Burnout Inventory Human Services Survey for Medical Personnel (MBI-HSS [MP]) [22]	✓	✓	✓
Absenteeism^a^	✓	✓	✓
Compassion fatigue: Professional Quality of Life Scale (ProQOL) Version 5 [54]	✓	✓	✓
Stigma: Measuring HIV Stigma and Discrimination Among Health Facility Staff: Standardized Brief Questionnaire [55]	✓	—	—
Anxiety: Generalized Anxiety Disorder (GAD-7) scale [56]	✓	✓	✓
Depression: Patient Health Questionnaire (PHQ-9) [57]	✓	✓	✓
Social support: Coping Orientation to Problems Experienced (COPE) Inventory [58]	✓	✓	✓
Optimism: Life Orientation Test – Revised (LOT-R) [59]	✓	✓	✓
Distress tolerance: Distress Tolerance Scale (DTS) [60]	✓	✓	✓
Acceptability: Client Satisfaction Questionnaire (CSQ-8) [61]^c^; Qualitative exit interviews^c^	—	✓	—
Adherence to Weekly Intervention Practice Exercises^a^^c^^d^	—	✓	✓

a Instrument developed by study team.

b Not available.

c Only for intervention arm.

d Will provide the research team with an understanding of whether intervention skills were implemented in nurse’s daily lives outside of the intervention setting and may be used to generate a rating of adherence to out-of-session practice guidelines during study analyses.

